**Fig. 1 Fig1:**
[figure not shown]
CONSORT study flow diagram for the trial protocol

### Blinding

All the primary and secondary outcomes will be assessed at each participating hospital by a single assessor, who will be blinded to group allocation. The patients themselves who are assessors of the patient-reported outcomes (the VAS score of back and leg pain, EQ-5D-5L score, and ODI score) are blinded (i.e., they are not informed of their assignment). The investigators of the patient-reported outcomes are also blinded.

Because blinding of patients is an integral part of this study, the research personnel and healthcare providers will not disclose surgical information to patients throughout the study. However, blinding may fail due to other available information such as operative time, size of the skin incision, and hospital cost. Therefore, patients will be asked to guess the surgery they underwent, and the extent of successful blinding will be assessed based on this parameter.

Postoperative surgical scarring, the extent of disc removed, and the presence/absence of injury to the facet joint on postoperative MRI or computed tomography (CT) images will be measured by a blinded assessor. Complications observed on simple radiographs, adverse events and the severity of these events, as well as surgery-related events, will be evaluated and managed by a blinded assessor. Surgeons will be made aware of the procedure performed (interlaminar full-endoscopic discectomy or microscopic discectomy) in each case. This information will not be revealed by either the participants or surgeons to the assessor. If unblinding is required, the assessor will be required to submit a justification to the trial team based on the assessment findings.

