#### Control intervention: conventional microscopic discectomy

For microscopic discectomy, the target lumbar level of symptomatic disc herniation is again visualized under C-arm intraoperative fluoroscopy, and a 2.5-cm midline incision is made over the target level. The paraspinal muscle is detached from the spinous process and lamina, and detached muscle towing is performed in a minimally invasive fashion through the small skin incision under microscopic visualization. Minimal laminotomy is then performed using a burr, and Kerrison punches under microscopic visualization. After the partial removal of the ligamentum flavum under the lamina, discal impingement of the spinal roots and dura is verified. The spinal nerve root is retracted using a root retractor, and the herniated disc is removed by pituitary forceps below the retracted nerve root. Following discectomy, the surgical field is verified for any remnant disc. This marks the end of the procedure.

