#### Primary outcome

The primary outcome will be the efficacy of the surgical intervention (interlaminar full-endoscopic discectomy or conventional microscopic discectomy), measured using the Oswestry Disability Index (ODI) score at 12 months [34, 35]. The ODI is the most valuable tool for evaluating patient-reported functional outcomes for lumbar spinal disabilities in a clinical setting [34, 35]**.** The ODI evaluates the level of function on activities of daily living for patients with low back pain across the following 10 areas: pain intensity, personal care, lifting, walking, sitting, standing, sleeping, sex life, social life, and traveling. Each section of the ODI is scored on a 5-point scale, with a score of 5 representing the most severe disability. The total ODI score is used for analysis, calculated as the sum of the scores across the 10 areas divided by the total possible score, and expressed as a percentage (i.e., multiplied by 100). For all unanswered questions, the total possible score is reduced by five. The highest score is recorded if the participant checks more than one answer. The ODI will be administered and scored by the assessor, which will be recorded in the eCRF system.

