#### Secondary outcomes

The following secondary outcomes will be included in the analysis: patient-reported outcomes, clinical outcomes, radiographic outcomes, and adverse events. Patient-reported outcomes are as follows: (1) presence and severity of low back pain and pain radiating to the lower-extremities, measured using a 10-point VAS score, ranging from “0” (no pain) to “10” (severe pain); (2) quality of life (QOL), measured using the EuroQol-5-dimension-5-level (EQ-5D-5L) questionnaire, which consists of five questions, with the total score ranging between “0” and “1,” with a higher score indicating a better QOL [36]; (3) satisfaction with the surgery; and (4) walking distance/time and time to return to daily activities after surgery. The following clinical outcomes will be measured: (1) postoperative surgical scarring, measured using the Patient and Observer Scar Assessment Scale (POSAS; version 2.0), which consists of six items scored on a 10-point system, with a score of “6” (i.e., a score of ‘1’ on each item) indicative of normal skin and a score of “60” (i.e., a score of “10” on each item) indicative of the “worst scar imaginable” and (2) surgery-related variables, namely postoperative drainage (mL), operative time (min), duration of hospitalization (h), and postoperative creatine kinase. The following radiographic outcomes will be obtained: (1) the extent of disc removed and injury to the facet joint, measured using postoperative MR or CT images, and (2) simple radiographs will be used for measuring other complications during the follow-up period. We will use the Carragee classification to evaluate MRI outcomes [37]. The dimensions of the disc on an axial image with the greatest encroachment will be directly measured [37]. The area of the herniated disc encroaching into the canal space (disc area) and hemiarea of the herniated disc (hemidisc area) will be calculated by using the following linear measurements on pre- and postoperative MRIs: 1) the longest anterior–posterior disc length and 2) width of the herniated disc at the midpoint of its posterior protrusion (mid anteroposterior disc width) [37]. To evaluate facet joint injury, the width of the medial facet on an axial image with the greatest width of the facet joint will be measured on pre- and postoperative MRIs [37]. Radiographs will be obtained in the anteroposterior, lateral, flexion, and extension views, and spondylolisthesis and segmental instability at the target surgical level will be scored based on these images. Radiographs will also be obtained at baseline and during each follow-up session. Preoperative spinal MRI will be systematically conducted in the sagittal and axial planes to determine the type and location of the disc herniation. Safety will be evaluated based on the number of adverse events and the severity of these events, as well as surgery-related events. Adverse events, including postoperative infection and recurrence of disc herniation, will be recorded at each follow-up session. Recurrence of disc herniation will be diagnosed on MRI when newly developed radiculopathy is suspected during the follow-up period. Adverse events will be reported to the surgeon by the participant or the assessor and will be recorded in the electronic database. The data on patient-reported outcomes, clinical outcomes, plain radiographs, and adverse events will be collected at baseline and at each follow-up session (2 weeks and 3, 6, and 12 months after surgery). The assessor will manage and evaluate outcomes and record them in the eCRF system (Table 1).

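### The one blinded assessor at each hospital rates scars that differ visibly by arm and also administers and scores the primary ODI

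*Protocol article*

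**What the plan says.** The Blinding section gives one person per hospital the whole outcome assessment and declares that person blinded: "All the primary and secondary outcomes will be assessed at each participating hospital by a single assessor, who will be blinded to group allocation". The Primary outcome section adds: "The ODI will be administered and scored by the assessor". The Secondary outcomes section lists POSAS scarring among the clinical outcomes and closes with a general statement of duties: "The assessor will manage and evaluate outcomes and record them in the eCRF system". Table 1 schedules POSAS at 12, 24 and 52 weeks. The third paragraph of Blinding confirms that scarring is measured by a blinded assessor.

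The two approaches leave different wounds. The section on the active intervention describes a 5–7 mm incision about 1 cm to the side of the midline. For the control, "a 2.5-cm midline incision is made over the target level".

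To protect the assessor, Blinding says that participants and surgeons will not reveal the procedure, and that a request to unblind must be justified to the trial team. To check blinding, it says that patients will guess which operation they had. No guess by the assessor is mentioned.

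**The concern.** The person declared blinded is required to inspect the feature that most plainly separates the arms, and the same person handles the primary endpoint. The Abstract and the Discussion both rely on blinding as a means of reducing bias. If the assessor knows the arm by 12 months, the primary comparison against the 12.8-point limit rests on assessor blinding that exists only in name. Because only patients are asked to guess, the loss would go unrecorded.

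**Working it through.** The plan gives no figure for this point, so there is none to reproduce. The check sets the sections side by side.

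**1. Does the scar show the arm?** Incision lengths, from the two intervention sections: 5–7 mm (endoscopic) and 2.5 cm = 25 mm (microscopic).
- 25 / 7 = 3.6
- 25 / 5 = 5.0

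The microscopic incision is 3.6 to 5 times as long and lies in the midline instead of about 1 cm beside it. Assuming that the healed scar keeps roughly the length and position of the incision, a rater who knows the two techniques can normally tell them apart.

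**2. Has the assessor seen the scar before the primary ODI?** Visit windows from Table 1:
- Visit 4: 12 ± 4 weeks, so weeks 8 to 16
- Visit 5: 24 ± 8 weeks, so weeks 16 to 32
- Visit 6: 52 ± 8 weeks, so weeks 44 to 60

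POSAS is due at all three visits. The latest in-window visit 5 (week 32) precedes the earliest in-window visit 6 (week 44) by 44 − 32 = 12 weeks. A participant who attends on schedule has therefore had two scar ratings before the 12-month ODI, whatever the order of tasks within a visit. For the week-12 ODI nothing firm can be said, because no within-visit order is stated. The 2-week ODI precedes any POSAS rating.

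**3. Does the stated safeguard help?** Non-disclosure governs what others say. It cannot hide a scar that the assessor has to rate.

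**4. Would a loss of blinding be noticed?** Only the patients' guess is collected, and it does not measure what the assessor knows.

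**5. By what route could it reach the ODI?** The patient supplies the answers. Scoring follows a fixed rule: item sum over possible total, the denominator cut by five for each unanswered item, and the highest mark taken when more than one is ticked. That leaves the assessor little judgement in scoring. What remains is influence while the questionnaire is administered, while a participant is helped to complete it, or during the phone interviews that Randomization and follow-up allows when attendance is impossible.

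**The case against.** Several points on the other side are sound, and they limit how far the criticism can go.

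- **The warning about cues concerns patients.** A reader might take "blinding may fail due to other available information such as operative time, size of the skin incision, and hospital cost" as an admission that the assessor will be unblinded. The sentence stands in a paragraph on patient blinding, is worded as a possibility, and leads to the patients' guess. Applying it to the assessor is an inference. The point above does not need it, because it rests on the incisions and the POSAS schedule.
- **Operative data.** A reader might infer that the assessor also sees operative time, since Secondary outcomes lists "surgery-related variables, namely postoperative drainage (mL), operative time (min), duration of hospitalization (h), and postoperative creatine kinase" and the general sentence on the assessor's duties follows. Nothing says who abstracts these data, and Data management has coordinators in each hospital managing the database. Nor does the document show that postoperative images identify the arm, or that the assessor learns the hospital cost.
- **Who assesses the ODI.** Blinding treats patients as the assessors of patient-reported outcomes, while Primary outcome has the assessor administer and score the ODI. This is not a true contradiction: a patient can answer a form that staff hand out and score. Self-completion is not excluded now.
- **Separate raters may be intended.** Randomization and follow-up speaks of an independent researcher, and the third paragraph of Blinding does not say that its blinded assessor is the same person. This leaves some doubt. The explicit wording, however, is one assessor per hospital for every outcome, and no division of roles is stated.
- **Operational detail.** The order of tasks within a visit and database permissions commonly sit in the full protocol, and their absence from an article is no error. The issue here is an allocation of tasks that the article does state and that does not fit the blinding it claims.
- **Putting a number on the bias.** A shift of, say, 2 to 4 ODI points would be 2/12.8 = 16% to 4/12.8 = 31% of the margin. Those points would be pure assumption, and no direction can be argued from the document.

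**Conclusion.** The point holds in a narrow form. As the tasks are written, the assessor can normally infer the arm before the 12-month ODI, the stated safeguard does not prevent it, and the planned check would not detect it. This rests on three assumptions: that the scar rater and the ODI assessor are the same person, as the text says; that scars keep the visible difference in length and position; and that participants attend at least one POSAS visit before month 12.

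A reader might go further and conclude that the primary result will be biased, or biased towards endoscopy. The document does not support that: patients are meant to be blinded, they provide the answers, and the scoring rule is fixed. The effect on the ODI has no derivable size or direction. This is a cheap improvement to the design, not an error that invalidates the endpoint.

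**What to change.** Amend Blinding and Primary outcome as follows.

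1. Participants complete the ODI, VAS and EQ-5D-5L unaided at every visit, and the entries are locked in the eCRF before any scar or imaging review. Self-completion is the essential part. Locking protects that visit's entries but cannot undo scar exposure from earlier visits.
2. Phone or assisted completion, and entry of operative data, go to existing site coordinators who do not rate the scar. Where possible, the coordinator who helps a participant should not be the one who entered that participant's operative data, since operative time could itself be a cue.
3. The assessor records a guess of allocation at 12 months, reported alongside the patients' guesses.

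If separate raters were already intended, the text should say so. The cost is a small change to visit procedure and eCRF permissions, with no extra staff. Some participants will still need help with the forms.

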### Measured outcomes

A complete description of the time-points at which the data on the primary and secondary outcomes will be collected is provided in Table 1.

**Table 1 Tab1:** Evaluation schedule

Visit type	Screening	Surgical intervention	Follow-up			
Visit	1	2	3	4	5	6
Visit week	4–0 weeks	0–2 days	2 weeks	12 weeks	24 weeks	52 weeks
			± 5 days	± 4 weeks	± 8 weeks	± 8 weeks
Informed consent	■					
Demographics^*^	■					
Inclusion/Exclusion	■					
Randomization		■				
Surgery		■				
MRI (or CT)†	■	■				
Simple radiographs	■		■	■	■	■
ODI	■		■	■	■	■
EQ-5D-5L	■		■	■	■	■
VAS	■		■	■	■	■
POSAS				■	■	■
Other survey‡			■	■	■	■
Adverse events		■	■	■	■	■

POSAS, Patient and Observer Scar Assessment Scale

^*^Baseline patient characteristics, including age, gender, occupation, comorbidity (diabetes mellitus, hypertension), bone mineral density, body mass index, medical/surgical history, smoking/drinking habits, physical examination, and laboratory test

^†^CT imaging used when MRI cannot be performed

^‡^Including surgery satisfaction, walking time/distance, and return to daily activities after surgery

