
### Statistical analyses

All statistical analyses will be performed using SAS Enterprise Guide 4 (SAS Institute Inc., Cary, North Carolina, USA). Before performing the main comparative statistical analyses, we will assess whether the baseline variables of the two groups are visually balanced.

An intention-to-treat strategy will be implemented in this non-inferiority RCT. In addition, sensitivity analyses using per-protocol and As-treated will be conducted to identify the deviations from the original assignments during randomization. Participants excluded before or after surgery will not be considered for analysis or replaced, thus avoiding the risk of bias in allocation concealment.

The primary outcome (the ODI score at 12 months post-surgery) will be compared between the two groups. Interlaminar full-endoscopic discectomy will be considered equivalent to microscopic discectomy concerning surgical outcomes if the 95% confidence interval (CI) of the treatment difference value of the Interlaminar full-endoscopic discectomy group is included in the equivalence limit of 12.8 points.

To analyze the time-dependent change in secondary patient-reported and clinical outcomes (i.e., VAS pain scores for the back and lower extremities and ODI, EQ-5D, and POSAS scores), a linear mixed model repeated-measures analysis of variance will be used. Time will be regarded as a categorical variable (at 2 weeks and at 3, 6, and 12 months) and analyzed to evaluate serial changes from baseline, within each group, and between the two groups at each session, with a post hoc test used for any significant time- and group-differences identified.

Chi-square test for categorical variables and Student’s t-test for continuous variables will be used to analyze other clinical and radiographic outcomes and adverse effects between the two groups. The collected data’s distribution will be evaluated using the Shapiro–Wilk test, with a two-sided P-value. Normally distributed continuous variables will be reported as means and standard deviations (SDs), with non-normally distributed continuous variables reported as medians and interquartile ranges. Categorical variables will be reported as count and percentage (%).

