### Sample size justification

In this trial, 100 participants will be recruited, with 50 in each group. Based on previous studies by Copay et al., the non-inferiority margin is 12.8 points and the maximal clinically accepted ODI difference is 12.8 points, with an SD of 17.1 points at 1-year after endoscopic discectomy [21, 35]. Based on the non-inferiority margin of 12.8, 50 participants will be required in each group, with an alpha value of 0.05, a power of 0.90, a one-sided 95% CI, and a loss to follow-up of 20%. Power Analysis and Sample Size software (version 15; NCSS, Kaysville, UT, USA) was used to calculate the sample size.

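### Facet-joint injury is a yes/no reading of the postoperative scan under Blinding but a pre/post width measurement under Secondary outcomes; the two must be reconciled, because variable type decides the test

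*Protocol article*

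**What the plan says.** Three sections of the protocol article bear on this outcome.

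- **Blinding.** Among the items a blinded assessor will measure is "the presence/absence of injury to the facet joint on postoperative MRI or computed tomography (CT) images".
- **Secondary outcomes.** The list of radiographic outcomes has "the extent of disc removed and injury to the facet joint, measured using postoperative MR or CT images", with no scale given. Further on, the same section gives a method: "To evaluate facet joint injury, the width of the medial facet on an axial image", taken on the image with "the greatest width of the facet joint will be measured on pre- and postoperative MRIs".
- **Statistical analyses.** The test follows the type of variable: "Chi-square test for categorical variables and Student’s t-test for continuous variables will be used to analyze other clinical and radiographic outcomes".

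A footnote to the evaluation schedule (Table 1) adds "CT imaging used when MRI cannot be performed". Table 1 places the imaging at screening and at the surgical visit (0 to 2 days).

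**The concern.** One named outcome is described in two ways that differ in scale (binary or continuous), in timing (postoperative only, or before and after) and in modality (MRI or CT, or MRI). No width change is given that would count as injury present, so the binary result cannot be derived from the width as the text stands.

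The description chosen decides whether the arms are compared by a difference in proportions with chi-square or by a difference in millimetres with a t-test. A postoperative reading taken alone also makes no stated use of the preoperative joint, although the trial images it. If the width change were reduced to yes/no for the comparison, information the trial already collects would be thrown away.

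**Working it through.** **Step 1. The descriptions side by side**

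| Feature | Blinding | Secondary outcomes, list | Secondary outcomes, method |
|---|---|---|---|
| Scale | present/absent | not stated | width (continuous) |
| Scan | postoperative | postoperative | pre- and postoperative |
| Modality | MRI or CT | MR or CT | MRI |
| Test under Statistical analyses | chi-square | undetermined | t-test |

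The difference is therefore within the document. It does not rest on something left out.

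**Step 2. What yes/no would cost if it were a cut of the width change**

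The plan has no figure for facet injury to reproduce. From the plan: 50 per arm ("100 participants will be recruited, with 50 in each group"). The postoperative scan falls within days of surgery, so 50 is used without the 20% loss allowed for the 12-month ODI. Assumed, because the document is silent: width loss is normal with equal SD, differs by d = 0.5 SD with less loss in the endoscopic arm, and is tested two-sided at 5%.

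*Continuous.* The standardised difference is d × √(n/2) = 0.5 × √25 = 2.5. Approximate power is Φ(2.5 − 1.96) = Φ(0.54) = 0.705. The exact t-test value is 0.70.

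*Yes/no.* Choose the cut-off c so that a proportion p of control patients is called injured: c = Φ⁻¹(1 − p). The endoscopic proportion is then 1 − Φ(c + d). Power is that of the uncorrected chi-square test, by exact enumeration of the two binomials.

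| Control injured | c | Endoscopic injured | Power, yes/no | Power, width |
|---|---|---|---|---|
| 50% | 0 | 1 − Φ(0.50) = 30.9% | 51% | 70% |
| 20% | 0.842 | 1 − Φ(1.342) = 9.0% | 37% | 70% |
| 10% | 1.282 | 1 − Φ(1.782) = 3.7% | 22% | 70% |

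**Step 3. How far the result moves with the assumptions**

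- d = 0.4: width 51%; yes/no 36%, 26% and 16% at control rates of 50%, 20% and 10%.
- d = 0.6: width 84%; yes/no 65%, 47% and 28%.
- d = 0.5 with *more* injury in the endoscopic arm: yes/no 51%, 46% and 38%, so the loss is smaller but still present.

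Power falls in every scenario. Its size depends on inputs that the document does not supply.

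**The case against.** The strongest reply is that the Blinding sentence says who reads the images and does not define an endpoint, whereas the Secondary outcomes section is where outcomes are defined and already names width as the means of evaluating injury. On that view the Blinding wording is a loose summary, and a yes/no result derived from width would be compatible with both sections. Much of this stands: it makes width the natural choice and the repair easy. It does not remove the mismatch, because the Blinding sentence still describes a binary reading of the postoperative scan, and nothing says which version is compared between arms.

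A second reply also stands. The power figures model a cut of the pre/post width change. They do not describe a separate visual reading of the postoperative scan, and they rest on assumed inputs. No power was claimed for this outcome.

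A reader might infer more than the text supports:

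- **That a real difference would probably be missed.** At a 50% control rate, yes/no power is 51% at 0.5 SD and 65% at 0.6 SD, so this does not follow in general.
- **That the analysts could report whichever version is favourable.** Nothing in the document shows such an intention, and a full protocol or SAP, not shown, may settle the choice.
- **That a naturally narrow facet could not be told from one cut at surgery.** Baseline MRI is scheduled, and nothing bars the assessor from consulting it.
- **That the claim of lesser invasiveness rests on the facet joint.** The Background's list of advantages over microscopic discectomy (incision, scarring, muscle damage, infection, blood loss, recovery, hospital stay) does not include it.

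**Conclusion.** The point holds as an inconsistency to be reconciled, and it is minor. The sections give different scales, timings and modalities for one secondary radiographic outcome, and the analysis rule sends the two versions to different tests. The reduction from about 70% to between 22% and 51% is conditional on Step 2's assumptions; it supports analysing the width as measured but is not an estimate for this trial. The primary ODI conclusion is unaffected.

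**What to change.** Name one analysed facet outcome in both Blinding and Secondary outcomes: the change in medial facet width, preoperative minus postoperative, in mm. In Statistical analyses, compare the arms with preoperative width as a covariate in place of the unadjusted t-test, and report the mean difference with its 95% CI.

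Remove the presence/absence wording from Blinding, or keep a yes/no count as descriptive only, derived from the width loss with a cut-off fixed before unblinding. State how patients imaged by CT instead of MRI enter the analysis, since the width method refers to MRI.

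The cost is a sentence or so in each section. For patients with MRI at both times, both widths are already planned, so no new visit or scan is needed. The downside is that the trial would report millimetres lost and have no tested headline injury rate.
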